### Data collection

The participants will be administered questionnaires at baseline (*T*_0_) and at two follow-up time point (*T*_1_=3 months and *T*_2_= 6 months). At baseline, the participants will undergo the MINI interview and there will be socio-demographic questions, including age, gender, and use of psychiatric services. The MINI is administered by the research assistant. All other questions will be self-administered and sent to the participant by e-mail at baseline and follow-up. All the participants will be allocated an individual trial identification number and all data will be collected in REDCap in a central computer storage under Mental Health Services in the Capital Region of Denmark.

To promote participant retention, robot-generated reminders will be sent out 1 week after the dissemination of questionnaires. If participants have not completed the questionnaire a week after the reminder was sent out, the research assistant will contact the participant and encourage them to answer the questionnaires and assist with any technical problems. All the participants will receive a minor gift card to a coffee shop once the questionnaire is completed. If a participant wishes to discontinue their participation, their data will be deleted. Still, the number of discontinuations will be reported in the Consort flow diagram. The Project Management Group is planned to meet on a weekly basis and the Trial Steering Committee will meet approximately every third month to review trial conduct and progress. The Ethical Committee and the independent Data Monitoring can review trial conduct throughout the whole trial period.

To secure data confidentiality, data on participants will be stored in a logged and closed computer drive in the Mental Health Services in Capital Region of Denmark. It will be stored until 5 years after the trial has finished. Afterwards, data will be permanently deleted.

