### Enrollment and randomization

Interested individuals will be encouraged to contact the research assistant through phone or e-mail. They will be provided with verbal and written information about the study, in which it is emphasized that participation is voluntary and that they may withdraw their consent at any time. They may take time to consider or discuss the participation with a next of kin before deciding whether to enrol in the study. During the enrollment phase, the potential participants will be interviewed by using the Mini-International Neuropsychiatric Interview (MINI) [32] and informed consent will be collected via an e-mail from REDCap [33] to the secure digital platform e-Boks where Danish citizens receive verified information [34]. The research assistant will make sure to get the informed consent in the enrollment phase. The participant information materials and informed consent form are available from the corresponding author.

After enrollment, participants will be administered the baseline questionnaires. Subsequently, they will be randomly assigned to either the intervention or the control group in a 1:1 allocation, using REDCap’s feature for a computer-generated sequence randomization. The randomization will be stratified by sex and number of NSSI episodes, as measured at baseline by the Deliberate Self Harm Inventory, to avoid overrepresentation of participants with a high number of NSSI episodes in one group. This stratification will be also facilitated through REDCap. The research assistant will generate the allocation sequence in REDCap after enrolling the participant and inform the participant which group, they are assigned to.

As part of the enrollment process, all participants will be informed that they can contact the research assistant in case of questions or technical problems. Participants will also receive information on where they can seek help if needed, for instance through helplines and the emergency services, such as 1318 and 112.

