### Statistical analysis

The analysis will be conducted according to the intention-to-treat principle. All participants will be included in the analysis according to group assignment, regardless of adherence. For the analysis of the primary outcome, the number of NSSI episodes during the preceding month, as measured at the 6-month follow-up, we will assess the intervention effect using linear regression with group allocation as the independent variable. If data from more than 5% of the participants are missing at 6 months, we will use multiple imputation to account for missing data. Imputation will be based on baseline NSSI, gender, age, and baseline variables associated with missingness. Secondary analysis will include baseline NSSI, age, gender, and baseline characteristics which differ between groups at baseline. Confidence intervals will be presented as well as significance level. All tests will be two-tailed and *p* values below 0.5 will be considered significant and interpreted with respect to the hierarchy of hypothesis recognizing that all outcomes, apart from the primary, are exploratory.

The analysis will be conducted using SPSS, version 22.0.

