Thirdly, the broad recruitment strategy might imply that participants using a range of mental health services will be included, which potentially could affect the treatment outcome. Persistent self-harm behaviours and more severe underlying psychopathology could affect the effect of the app. By collecting information on the received treatment, we can adjust for this in the analysis. However, there might be a difference in how the general experience of the app is, depending on the knowledge level of NSSI and the degree and duration of the NSSI. The broad variation of participants, which includes both individuals with milder symptoms of NSSI and more severe and chronic NSSI, can make it difficult to distinguish a potential difference in maybe the usage of the app, how relevant the app is perceived and the outcome of the app. Also, specialized treatment for NSSI is an exclusion criterion which can furthermore make the recruitment more difficult.

The questionnaires in the trial cover different topics such as NSSI, suicidal ideation, depressive symptoms, and self-esteem which for some of the participants can be difficult to reflect on and quantify. Avoidance of these topics might occur and make it more difficult to get the questionnaires answered, especially since it is self-administered questionnaires. The questionnaires are sent out three times with a 3-month interval and that can also be an obstacle since it requires time and effort which can lead to participant dropout.

Finally, neither the participants nor the research assistant will be blinded to the assignment of treatment condition due to the nature of the intervention. However, the research assistant will remain blinded during the analysis and drafting of the manuscript.

A worsening of the condition of a participant may occur during the trial. To ensure the participants know where to seek help, the research assistant will inform all participants in the enrollment process about relevant support options. As part of the onboarding process, the intervention group will be offered an introduction by phone on how the app can be used as a safety plan and important phone numbers to emergency services are pre-installed in the app, etc. The research assistant will be available to answer questions regarding the app or the questionnaires and give technical support throughout the trial.

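### Deleting the data of participants who withdraw contradicts the promised intention-to-treat analysis of everyone randomised

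*Protocol article*

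**What the plan says.** The Data collection section of the protocol article sets the rule for people who leave: "If a participant wishes to discontinue their participation, their data will be deleted". It continues: "Still, the number of discontinuations will be reported in the Consort flow diagram". No exception is made for baseline or 3-month answers already given.

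The Statistical analysis section states "The analysis will be conducted according to the intention-to-treat principle" and "All participants will be included in the analysis according to group assignment, regardless of adherence". For missing outcomes it says "If data from more than 5% of the participants are missing at 6 months, we will use multiple imputation to account for missing data", and then "Imputation will be based on baseline NSSI, gender, age, and baseline variables associated with missingness".

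Two other places bear on this. Enrollment and randomization tells candidates that "participation is voluntary and that they may withdraw their consent at any time", and places the baseline questionnaires before randomisation. The Discussion expects some loss, because answering the questionnaires repeatedly is a burden: "it requires time and effort which can lead to participant dropout". It gives no rate.

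**The concern.** Baseline data are collected before allocation. Anyone who withdraws after allocation is therefore a randomised participant with baseline NSSI count, sex and age on file. The deletion rule removes that person from the analysis set that the statistical section defines, and removes the predictors that the imputation model needs. It also removes any 3-month DSHI answer. That answer is not among the listed imputation predictors, but it would be the most recent information on the primary outcome for a sensitivity analysis.

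At stake is whether the primary comparison is between the groups as randomised or between those who stayed. Participants are not blinded, the controls are on a waitlist, and the Discussion concedes that the app might maintain or worsen NSSI. Leaving could therefore be related to both arm and outcome. The missing-data rule may also be affected: the article does not say whether its 5% is a fraction of all randomised or of the records that remain.

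**Working it through.** **1. The two rules, case by case**

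| Participant after randomisation | Record kept? | Analysed as assigned? | Imputable from baseline? |
|---|---|---|---|
| Stops using the app, answers questionnaires | yes | yes | not needed |
| Does not answer at 6 months, no withdrawal | yes | yes, by imputation if the 5% rule is met | yes |
| Says they wish to discontinue | no, only counted | no | no |

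The contradiction lies in the third row alone. No other section limits deletion to people who ask for erasure, and none restricts the analysis set to those whose data remain.

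**2. The planned sample size**

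Inputs from the Sample size section: difference 3.5, SD 9, power 90%, type I error 0.05. Tests are two-tailed (Statistical analysis section).

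n per arm = 2 × SD² × (1.960 + 1.282)² / difference² = 2 × 81 × 10.51 / 12.25 ≈ 139 by the normal approximation. The two-sample t test needs 140 (power 0.898 at 139, 0.900 at 140). The stated 140 per arm reproduces, and it is a number of analysed participants with no allowance for loss.

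With assumed loss at the same rate in both arms, power by the normal approximation is:

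| Lost | Per arm | Power |
|---|---|---|
| 5% | 133 | 0.89 |
| 10% | 126 | 0.87 |
| 20% | 112 | 0.83 |
| 30% | 98 | 0.78 |

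Most of this loss comes from the missing 6-month outcome itself. Keeping the baseline record and imputing would recover only part of it.

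**3. The 5% rule (assumed counts)**

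Suppose 30 of 280 withdraw and are deleted, and 10 of the other 250 do not answer at 6 months.

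- Counted on the remaining file: 10/250 = 4.0%, below 5%, so no imputation.
- Counted over all randomised: (30 + 10)/280 = 14.3%, so imputation is triggered.

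**4. Possible bias (assumed values)**

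Let a fraction d of an arm be deleted, and let those people average k more episodes at 6 months than those retained, whose mean is m. The full-arm mean is (1 − d)m + d(m + k) = m + dk, so the retained mean is too low by dk. With the same k in both arms, the app-minus-control estimate shifts by −(d_app − d_control) × k.

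| d app | d control | k | Shift in episodes |
|---|---|---|---|
| 10% | 0% | 8 | −0.8 |
| 20% | 10% | 9 | −0.9 |
| 30% | 10% | 9 | −1.8 |
| 10% | 20% | 9 | +0.9 |
| 20% | 20% | 9 | 0 |

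A negative shift favours the app. The first row is 0.8/3.5 = 23% of the target difference. The last two rows show that the sign can reverse and that the shift can vanish.

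**The case against.** The strongest reply is that the rule is narrow. It is triggered by a wish to discontinue, which can be read as the withdrawal of consent described under Enrollment and randomization. The same paragraph handles non-response separately, with a reminder and then contact by the research assistant. The dropout that the Discussion expects is mainly unanswered questionnaires, and those records stay. This stands: the conflict is limited to active withdrawals. It does not remove the conflict, because the article still ties deletion to the wish to stop and not to a request for erasure.

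A second reply is that deletion may have been promised to participants. The consent form is not shown, so this cannot be excluded. The article itself cites no duty to erase. If there was such a promise, the statement that all participants are analysed would be the part to correct.

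Third, the 5% rule speaks of participants, and the number of discontinuations is kept, so the rule can be applied to all randomised. That is fair: the denominator is unspecified, not shown to be wrong. The deleted people in the example could not be imputed whichever way it is counted; the trigger decides only how the 10 non-responders are handled.

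A reader might also infer that no sensitivity analysis is possible for those removed. That goes too far. If deletions are counted by arm, their effect can be bounded. What is lost is any analysis that uses those participants' own data.

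**Conclusion.** The contradiction is on the face of the text and is certain: the Data collection and Statistical analysis sections cannot both be followed for a randomised participant who withdraws. It should be corrected, because it determines who is in the primary analysis.

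The size of the consequence is unknown. The article gives no withdrawal rate, no reasons and no difference between arms. Every figure in steps 3 and 4, and each loss rate in step 2, is an assumption for illustration. A reader might infer that those who withdraw are the most informative dropouts, or that deletion favours the app. The documents support neither. They make withdrawal related to arm and outcome plausible, but disappointment on the waitlist could remove controls and push the estimate the other way, and equal loss with equal excess gives no shift. Retention would not guarantee an unbiased result either: imputation from baseline corrects only for what baseline explains.

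**What to change.** 1. After a check of the consent text, reword the Data collection rule so that data collected up to withdrawal are kept and analysed unless the participant explicitly asks for erasure.
2. State that the 5% threshold is counted over all randomised participants, including those deleted.
3. Report deletions by arm in the CONSORT diagram, not only in total.
4. Add a sensitivity analysis that bounds the effect of deleted participants, over a range of assumed 6-month means set separately for each arm. The range has to be fixed before unblinding, since an episode count has no natural upper limit.
5. Where records have already been erased, or erasure was promised, state that the primary analysis excludes those participants and is not a full intention-to-treat analysis.

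The cost is protocol wording, the consent check, a flag in REDCap that separates withdrawal from erasure, and one extra analysis. According to Trial status, enrolment ran until September 2023 and the last questionnaire was due on 22 February 2024. Step 1 can therefore protect only records not yet erased; anything already deleted cannot be recovered. Steps 2 to 5 remain possible if the number deleted in each arm is known.

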### Sample size

Based on previous estimates, a reduction of 3.5 NSSI episodes is expected in the intervention group after the 6-month follow-up compared to participants in the waitlist control group at follow-up after 6 months [28, 43, 44]. A post-intervention standard deviation of 9 is assumed based on previous findings [43, 44]. If the true difference between the intervention and control groups is 3.5, a total of 140 participants should be included in each group in order to reject the null hypothesis with a power of 90% and a type I error probability of 0.05, implying a total of 280 participants.

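### The 280 participants give 90% power only if every one supplies the 6-month outcome; the sample size makes no allowance for missing outcomes

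*Protocol article*

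**What the plan says.** The Sample size section sets out its assumptions. The difference is conditional: "If the true difference between the intervention and control groups is 3.5". The spread comes from earlier work: "A post-intervention standard deviation of 9 is assumed based on previous findings". From these it concludes that "a total of 140 participants should be included in each group in order to reject the null hypothesis with a power of 90" per cent and "a type I error probability of 0.05, implying a total of 280 participants". The Abstract and the opening of Methods and design also give 280 as the number to be included, and Table 1 gives it as the target. No attrition rate or inflation factor appears anywhere in the article.

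Other sections do not assume complete follow-up:

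- The Discussion says of the repeated questionnaires that "it requires time and effort which can lead to participant dropout", and that participants may avoid the topics.
- Data collection describes reminders, personal contact and gift cards to support retention. It also says that the data of a participant who discontinues are deleted.
- Statistical analysis says: "If data from more than 5% of the participants are missing at 6 months, we will use multiple imputation". The imputation uses baseline variables, including baseline NSSI.

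The primary model is a linear regression with group allocation as its only independent variable. Baseline NSSI enters a secondary analysis.

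**The concern.** A number needed for analysis has been used as the number to recruit. The two agree only if every randomised participant answers the 6-month Deliberate Self Harm Inventory, and the rest of the article does not plan on that. The primary model, as stated, gains no precision from a covariate that might absorb some loss.

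What is at stake is how the result is read. If the trial finds no difference, readers will take it as coming from a trial with 90% power to detect 3.5 episodes. With any appreciable loss to follow-up the real figure is lower, and the article gives no means of judging by how much.

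**Working it through.** **Inputs.** Difference 3.5, SD 9 (taken as common to both arms), power 90% and alpha 0.05, all from Sample size. Two-sided, from Statistical analysis ("All tests will be two-tailed"). Equal allocation, from Enrollment and randomization ("randomly assigned to either the intervention or the control group in a 1:1 allocation"). Missing rates and baseline–outcome correlations are not in the protocol; those below are assumptions.

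**Step 1: reproduce the stated figure.**

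n per arm = 2 (1.960 + 1.2816)² × 9² / 3.5² = 2 × 10.508 × 81 / 12.25 = 138.96, so 139 by the normal formula.

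The two-sample t test (non-central t) gives 89.8% with 139 per arm and 90.0% with 140. So 140 is the smallest number per arm that reaches 90%, and it contains no hidden allowance. A one-sided calculation gives 114 and does not match.

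**Step 2: power if missing participants contribute nothing.** The same rate d is assumed in both arms, so the analysed number is 140(1 − d). The detectable difference at 90% power is 3.2416 × 9 × √(2/n), by the normal formula.

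| Missing (assumed) | Analysed per arm | Power, t test | Detectable difference |
|---|---|---|---|
| 0% | 140 | 90.0% | 3.5 |
| 5% | 133 | 88.5% | 3.6 |
| 10% | 126 | 86.8% | 3.7 |
| 20% | 112 | 82.6% | 3.9 |
| 30% | 98 | 77.3% | 4.2 |

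Power reaches about 80% at 25% missing (105 per arm, 80.1%) and falls below it just beyond. The normal approximation runs 0.2 to 0.4 points higher than the t test in this table (82.9% at 20%, 77.7% at 30%). Steps 3 and 4 use the normal approximation.

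**Step 3: power with the planned imputation.** Assume outcomes missing at random, baseline NSSI retained, and correlation r between baseline and 6-month NSSI. The variance of the unadjusted difference after imputation is approximately

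V = (2 × 81/140) × [(1 − r²)/(1 − d) + r²], and power = Φ(3.5/√V − 1.960).

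For example, with r = 0.5 and d = 0.20 the bracket is 0.75/0.80 + 0.25 = 1.1875. Then V = 1.1571 × 1.1875 = 1.374, √V = 1.172, and power = Φ(2.986 − 1.960) = 84.8%.

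| Missing | r = 0.3 | r = 0.5 |
|---|---|---|
| 20% | 83.6% | 84.8% |
| 30% | 78.8% | 80.8% |

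Against 82.9% and 77.7% without imputation, the gain is 0.7 to 1.9 points at 20% missing and 1.1 to 3.1 points at 30%. It does not apply to participants whose data are deleted, since no baseline record remains from which to impute.

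**Step 4: power if the primary model adjusts for baseline NSSI.** The residual SD is 9√(1 − r²), which is 8.59 for r = 0.3 and 7.79 for r = 0.5. The analysed number is 140(1 − d).

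| Missing | r = 0.3 | r = 0.5 |
|---|---|---|
| 20% | 86.2% | 91.9% |
| 30% | 81.4% | 88.2% |

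**The case against.** The strongest reply is that the calculation is right and its power is stated conditionally. The protocol gives no dropout rate. The Discussion says only that dropout can happen, in a paragraph on limitations, and the 5% rule is itself an if-clause. Retention measures are in place. At 5% missing the loss is only about 1.5 points; losses of 10 points or more need rates near 30%, which nothing in the article supports. All of this stands. A reader might infer that the trial is underpowered, that it lacks its stated power as a matter of fact, or that the sponsor expects substantial dropout. The documents support none of these: each needs a rate they do not give.

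A second objection is that complete-case power describes an analysis the plan would not run, since imputation starts above 5% missing. That is fair, and Step 3 shows the imputed figures. Recovery is partial, and there is none for deleted records.

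A third is that little can change now. Trial status puts the end of recruitment at September 2023 and Table 1 lists the trial as not recruiting. The planned confidence intervals will show what a null result can exclude, and loss of precision alone invalidates neither the estimate nor the type I error. This limits the seriousness, but it does not justify leaving the 90% unqualified.

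The article condenses a fuller protocol that is not shown. That does not remove the point, because the article itself ties 90% power to the number included.

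**Conclusion.** The point holds in a conditional form. The arithmetic in Sample size is correct; the fault is that the number to analyse is used as the number to include, with no margin. The stated 90% therefore applies only with complete 6-month data, a condition the article does not state and elsewhere does not rely on.

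The shortfall is negligible to moderate at low rates (1.5 points at 5% missing, 3 at 10%) and material at higher ones (7 points at 20%, 13 at 30%, before any imputation). These sizes rest on assumed missing rates equal in both arms and on the protocol's own difference and SD. The imputed and adjusted figures also assume data missing at random and a correlation of 0.3 to 0.5. The correction is worth making because it is cheap and bears on how a null result is read. It is not a reason to call the design invalid.

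**What to change.** 1. Restate the conclusion of Sample size along these lines: *280 participants give 90% power if all provide the 6-month outcome.*
2. Add power over a range of missing rates, labelled as assumptions: about 88% at 5%, 87% at 10%, 83% at 20% and 77% at 30% where the missing participants contribute nothing; about 84–85% at 20% and 79–81% at 30% under the planned imputation with a correlation of 0.3 to 0.5.
3. Consider making the baseline-adjusted model primary, decided and recorded before group codes are unmasked. Baseline NSSI is already collected and is a stratification factor. This would offset part or all of the loss: at 20% missing about 86% (r = 0.3) to 92% (r = 0.5), and at 30% missing about 81% to 88%. Show both ends of the range, since the correlation is assumed.

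Items 1 and 2 cost a few sentences. Item 3 changes the primary model but needs no new data. No further enrolment is asked for.
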